#### General

•Complications: Complications resulting from the application of the different treatments will be monitored to identify potential differences in the occurrence or severity of complications between treatments.

•Re-interventions/Secondary surgery: One of the goals of the conservative treatment policy is to avoid surgery while still achieving fracture healing and a favourable clinical outcome. The rate of secondary surgery is hence an indication of the success or failure of this policy. Secondary interventions and the cause/motivation for its application will therefore be monitored.

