**Methods/Design:**

The trial is an observational study in which eleven centres in five European countries are involved. All patients admitted to one of these centres who meet the selection criteria (≥55 years, acute (<two weeks) type II/III odontoid fracture, no rheumatoid arthritis, no ankylosing spondylitis, no previous treatment for odontoid fracture) are asked to participate. The applied treatment is in accordance with usual care and chosen by the treating surgeon and patient. A cohort of 275 patients will be included. Clinical and radiological follow-up moments are scheduled at 6, 12, 26, 52 and 104 weeks, at which both surgeon and patient will complete Case Record Forms (CRFs). The primary outcome will be a combination of fracture healing and clinical outcome at 52 weeks. Osseous union and fracture stability will be assessed with CT-imaging and dynamic X-ray. Clinical outcome will be scored by the Neck Disability Index (NDI) and correlated to the imaging data. Additionally, predefined subgroup analysis will be carried out (i.e. for patient age and osteoporosis) and prognostic factors will be identified.

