## Background

In the elderly, odontoid fractures are the most common fractures of the cervical spine [1-6]. As the population ages, their incidence and relevance to clinical practice are expected to increase [7]. The treatment for patients with fractures of the odontoid process is based on the fracture pattern, the patient’s medical condition [2] including age, pain, neurological deficits, and the surgeon’s personal preference. Surgical treatment involves anterior odontoid screw fixation or posterior (cranio)atlanto-axial arthrodesis, leading to prompt stability of the upper cervical spine. However, the condition of the patient may deteriorate by undergoing (major) cervical spine surgery [8]. Especially in the very old (≥80 years of age), a surgical intervention has significant risks for the patient. An alternative to avoid the possible complications of cervical spine surgery is conservative treatment with rigid or non-rigid immobilisation for a longer period of time. However, such immobilisation may eventually result in non-union and prolonged fracture instability, requiring secondary surgery [9]. This unnecessarily lengthens treatment duration and, worse, can cause significant deterioration of the cervical spine anatomy and the patient’s condition [10].

Finding the right balance between fracture healing and treatment complications is difficult. In very old patients, finding this balance is even more challenging. In hospitals where upper cervical spine surgery is frequently performed, it is becoming increasingly common to operate on even the very old patient with a cervical spine fracture. However, debate remains as to whether or not this is indeed a favourable development.

Currently available literature reviews on this topic were inconclusive [11,12]. Recent clinical studies focussed on survival and the occurrence of complications, but not on fracture union and stability [13,14]. All other performed clinical studies were carried out retrospectively, were of limited quality and most did not specifically focus on elderly patients. Moreover, minimal attention was paid to grounds for chosen treatments, and patient groups were often poorly comparable. In the vast majority of published studies, only a small number of patients were included (typically <50).

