### Treatment

The treating surgeon and patient will make a shared decision as to whether surgical or conservative treatment will be applied. Participating centres and surgeons are all able to facilitate and respectively carry out both surgical and conservative treatments.

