### Follow-up period

Patients will be seen by the treating surgeon five times for radiological and/or clinical follow-up visits; at 6, 12, 26, 52 and 104 weeks after the start of treatment. In addition to usual patient care, patients will be sent questionnaires (CRFs) to complete at home prior to each follow-up visit (Table 3). On no occasion will patients see the results of earlier assessments. After the last follow-up visit at 104 weeks the patient’s participation in the study ends.

**Table 3 T3:** Data collection and outcome measures

	**Baseline**	**Immediately after start of treatment**	**Weeks of follow-up**				
			**6**	**12**	**26**	**52**	**104**
General status and fracture assessment	**X**						
Demographic data	**X**		**X**	**X**	**X**	**X**	**X**
NDI, MDI, VAS neck pain, SF-36, EQ-5D	**X**	**X***	**X**	**X**	**X**	**X**	**X**
DS14, IPQ-K, Likert			**X**	**X**	**X**	**X**	**X**
Complications of surgery		**X****	**X****	**X****	**X****	**X****	**X****
Secondary surgery			**X****	**X****	**X****	**X****	**X****
Dynamic X-ray					**X**	**X**	**X**
CT-Cervical spine	**X**			**X**	**X****	**X**	

*In case of surgical treatment only.

**When indicated.

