### Data analysis

Data analysis will be carried out based on the intention-to-treat principle. Cross-over-cases (e.g. surgery after failed conservative treatment) will be analysed among the original treatment group. This will not cause methodological problems because it is two healthcare strategies that are being compared, as opposed to two specific treatments. The reasons for cross-over of patients will be studied and reported. Causes of death will be analysed and a potential relation to the diagnosis and the applied treatment will be studied.

As-treated analysis will additionally be carried out in a sensitivity analysis and prognostic factors for the likeliness of surgery after failed conservative treatment will be studied.

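### The complications outcome admits only events judged to result from treatment, with treatment known, and Table 3 schedules only surgical complications; ascertainment may differ between groups and bias the comparison

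*Protocol article*

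**What the plan says.** All references are to the protocol article.

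- **Secondary outcome, General.** The outcome is defined by cause: "Complications resulting from the application of the different treatments will be monitored". Its purpose is comparative: "to identify potential differences in the occurrence or severity of complications between treatments".
- **Table 3 (Follow-up period).** The only complications row is labelled "Complications of surgery". Every marked cell, from the start of treatment to week 104, carries the footnote "When indicated". No row covers complications of a collar or halo, or general medical events.
- **Treatment.** "The treating surgeon and patient will make a shared decision as to whether surgical or conservative treatment will be applied". The abstract adds that surgeon and patient both fill in the CRFs.
- **Data analysis.** Cross-overs stay in their original group because "it is two healthcare strategies that are being compared, as opposed to two specific treatments". Causes of death are analysed, and a possible relation to diagnosis and treatment is then studied.
- **Background.** On surgery, it warns that "the condition of the patient may deteriorate by undergoing (major) cervical spine surgery". For conservative treatment, the main harm named runs through failed healing and later surgery.

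**The concern.** The definition places a causal judgement between an event and its being counted. Whoever makes that judgement is likely to know the treatment, since it is neither randomised nor concealed. In an elderly cohort, events such as pneumonia, delirium or a fall can be put down to an operation, to immobilisation, or to age and frailty. If the share accepted as treatment-related differs between groups, the recorded rates differ even where the true risks are equal, or a real difference is masked.

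Table 3 adds a second route to the same problem. A row that names only surgery, completed only when indicated, may prompt fuller recording in the surgical group. Correcting the row label alone would leave the causal filter in place.

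The Background presents the balance between healing and treatment complications as the central difficulty, above all in the very old. An event left off the CRF cannot be recovered by any later analysis.

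**Working it through.** The plan states no complication rate, attribution share or power for this outcome, so there is no figure of its own to reproduce. The check is first textual, then illustrative.

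**1. Passages side by side**

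| Place | What it implies |
|---|---|
| Secondary outcome, General | Both treatments are covered, but only events caused by them |
| Table 3 | Only surgical complications are scheduled, when indicated |
| Data analysis, strategies | The comparison is of whole strategies, so events under a strategy matter whatever their cause |
| Data analysis, deaths | Causes are analysed and the relation to treatment studied afterwards, with no causal filter at entry |

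The first two rows disagree on scope. The last two show the article using a broader approach elsewhere.

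**2. How unequal attribution acts**

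Let r be the true risk, equal in both groups, and q_S and q_C the shares attributed to treatment in the surgical and conservative groups. The recorded risks are p_S = r × q_S and p_C = r × q_C. The recorded risk ratio is p_S / p_C = q_S / q_C, whatever r is. It is 1.00 when the shares are equal.

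**3. Illustration**

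From Sample size: 275 patients, 10% dropout, 2:1 surgical to conservative. So 275 × 0.9 = 247.5, or about 165 surgical and 82 conservative. Assumed, with no source in the article: r = 30% and every q.

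The chance of p < 0.05 (two-sided) is Φ[(|p_S − p_C| − 1.96 × SE0) / SE1], where SE0 uses the pooled proportion and SE1 the separate ones. For q_S = 80% and q_C = 40%:

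- p_S = 0.30 × 0.80 = 0.24 and p_C = 0.30 × 0.40 = 0.12.
- Pooled proportion = (165 × 0.24 + 82 × 0.12) / 247 = 0.200.
- SE0 = √[0.200 × 0.800 × (1/165 + 1/82)] = 0.0541.
- SE1 = √(0.24 × 0.76/165 + 0.12 × 0.88/82) = 0.0489.
- (0.12 − 1.96 × 0.0541) / 0.0489 = 0.29, so the chance is about 61%.

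| q_S / q_C | Recorded, surgical v conservative | Risk ratio | Chance of p < 0.05 |
|---|---|---|---|
| 70% / 70% | 21% v 21% | 1.00 | 5% |
| 80% / 60% | 24% v 18% | 1.33 | 18% |
| 80% / 40% | 24% v 12% | 2.00 | 61% |
| 90% / 30% | 27% v 9% | 3.00 | 94% |

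For true risks of 10% to 40%, the 80% / 40% case gives false differences of 4 to 16 points and a 19% to 78% chance of p < 0.05.

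The direction is as open as the size. If surgeons were slower to blame their own operations and the shares were 40% / 80%, the recorded rates would be 12% v 24% and the risk ratio 0.50.

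**4. Limits of the illustration**

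It allows each patient at most one event. A patient with several events is recorded if any one is attributed, which would narrow the gap. It also removes dropouts, although complications are collected from the start of treatment.

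**The case against.** A reader might infer that general medical complications will be credited more readily to surgery and that the harm comparison is therefore distorted. The article does not support that. It does not say who attributes a complication or by what rule, and nothing in it shows that attribution will differ. A surgeon judging their own operation could attribute too little. The figures above restate assumed shares and are not evidence of bias. This part of the objection stands.

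Other arguments on the same side:

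- **The article is condensed.** Event lists and relatedness rules may sit in the full protocol or CRF, and their absence here is no fault. That stands, but the point rests on what the article does state: a causal restriction in the definition and a surgery-only row in the schedule.
- **Other measures escape the filter.** Deaths, secondary surgery and the patient-reported scales (NDI, SF-36, EQ-5D) are not limited to treatment-attributed events. That stands; only part of the harm picture is exposed. Complications are also a secondary outcome, and the univariate analyses listed name no test for them.
- **An all-cause count has its own bias.** Treatment depends partly on medical condition and age, so counting every event brings in baseline frailty differences between non-randomised groups. That stands and has to be met by adjustment. It does not favour filtering at entry, because recording all events with attribution as a separate item keeps both counts available.

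**Conclusion.** The point holds as a risk of bias, not as a demonstrated distortion. The stated definition admits only treatment-attributed complications, the judgement is likely to be made with treatment known, and the schedule names only surgical complications. Together these allow attribution and ascertainment to differ between groups. A bias against surgery is plausible, given the surgery-only row and the Background's emphasis on harm from surgery, but neither direction nor size can be established from the article. The illustrated effect runs from none with equal attribution to a doubled recorded risk with 80% against 40%, and rests wholly on assumed shares. The definition also fits poorly with the article's own statement that strategies are compared and with its handling of deaths. The change is inexpensive and worth making; the primary outcomes are not affected.

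**What to change.** - Reword the complications item under Secondary outcome, General, so that every new medical or local complication is recorded in both groups whatever its judged cause.
- Replace the surgery-only row in Table 3 with one covering all complications in both groups at the same visits, and bring the CRF into line where it does not already do this.
- Record attribution to treatment as a separate CRF item.
- Compare the groups on all complications, adjusted with the propensity score already planned under Multivariate analysis. Report treatment-attributed complications alongside, as descriptive.

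The cost is protocol and CRF wording and more events to record. The main count becomes less specific to treatment and will include background events and baseline frailty differences, hence the adjustment. That adjustment may be incomplete: the listed baseline variables include age, SF-36 and EQ-5D but no direct measure of comorbidity or frailty.

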### Sample size

Based on the recent literature review, the estimated possible difference in fracture union between the groups is 41% and in fracture stability this difference is 21% [12]. For both union and stability, however, a smaller difference of 20% would be clinically relevant and the study is powered to assess this difference. For the NDI, a 7.5 point difference (on a 50 point scale) is generally accepted as a minimal clinically important difference with a SD of approximately 10 in various psychometric studies [26-29]. Furthermore, it is expected that the number of patients that will be treated surgically will be twice the number of patients that are treated conservatively (2:1) [14]. Since three primary outcome hypotheses will be tested, the significance level (α) has to be divided by three. Based on the primary outcome parameters, the required sample size, assuming α = 0.05/3 = 0.0167 (two-sided) and β = 0.20 (80% power) and an expected drop out rate of 10%, is 275 for union, 198 for stability and 93 for the NDI. In conclusion, 275 patients will need to be recruited in order to give a reliable conclusion to the comparison of union, stability and clinical outcome between the surgically and conservatively treated groups.

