#### Univariate analysis

Univariate analysis will be carried out using χ^2^-tests for dichotomised outcomes and T-tests for continuous outcomes. Intention-to-treat analysis will be used for cases that crossed over to other interventions.

•Primary analysis

The χ^2^-test will be used to test for differences between groups on union and stability at 52 weeks (α = 0.0167). T-test will be used to test for differences between groups on NDI improvement at 52 weeks (α = 0.0167).

•Secondary analysis

The χ^2^-test will be used to analyse the difference in dichotomised NDI. NDI will be dichotomised using the criterium of the minimal clinically important change (improvement) of 7.5 points out of 50. The relation between radiological parameters (union and stability) and NDI will be analysed by comparing the average NDI improvement for patients that acquired union/stability with those that did not.

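### A fixed 0.0167 for each primary test is valid, but Holm's procedure controls the same 5% family-wise error and can give up to about 9 points more power for union

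*Protocol article*

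**What the plan says.** The article names three primary outcomes at 52 weeks: union, stability and improvement in NDI. Its Primary outcome section notes that the significance level was adjusted for them.

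The Sample size section gives the rule: "Since three primary outcome hypotheses will be tested, the significance level (α) has to be divided by three". The numbers are computed "assuming α = 0.05/3 = 0.0167 (two-sided) and β = 0.20 (80% power"), with 10% drop-out, and come to 275 for union, 198 for stability and 93 for NDI. Union therefore sets the target. The design effects are 20 percentage points for union and for stability ("a smaller difference of 20% would be clinically relevant and the study is powered to assess this difference") and 7.5 NDI points with SD 10. The expected split is 2:1, surgical to conservative.

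The Univariate analysis section carries the same level into each test. For the two binary outcomes: "The χ^2^-test will be used to test for differences between groups on union and stability at 52 weeks (α = 0.0167"). For NDI: "T-test will be used to test for differences between groups on NDI improvement at 52 weeks (α = 0.0167"). No step-down, hierarchical or alpha-recycling rule appears, so the article fixes plain Bonferroni for the analysis as well as for the sizing.

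**The concern.** Family-wise control at 0.05 over three tests needs only the smallest p-value to meet 0.0167. Once that hypothesis is rejected, Holm compares the next p-value with 0.025 and the last with 0.05. It holds the family-wise error at 0.05 under any dependence between the outcomes, which matters because union, stability and NDI are plausibly correlated. It requires no ranking of the outcomes.

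Union is where the choice can matter. At the 20-point difference it has only the planned 80% power, whereas 275 patients are more than stability and NDI need. When those two are rejected, Holm tests union at 0.05, while the article's rule keeps it at 0.0167. At stake is a real 20-point difference in union, which the article calls clinically relevant, being missed more often than the overall error rate requires.

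**Working it through.** **Inputs from the Sample size section.** Two-sided α = 0.05/3 = 0.0167; power 80%; 2:1 split; 20 points for union and stability; 7.5 points and SD 10 for NDI; 10% drop-out; 275 recruited. Evaluable: 275 × 0.9 = 247.5, that is 165 v 82.5 (simulated as 165 v 83).

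**Assumed inputs.** The rates behind the 20-point differences are not stated. I used union 77% v 57% and stability 89% v 69%, because they return the article's totals.

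**Reproducing the stated sizes.** The normal quantiles are 2.394 (two-sided 0.0167) and 0.842 (80% power).

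- NDI, conservative arm: (2.394 + 0.842)² × 10² × 1.5 / 7.5² = 27.9, so 28. With 56 surgical the total is 84, and 84 × 1.1 = 92.4, so 93, as stated.
- Union, conservative arm: n = [2.394·√(3·p̄·(1−p̄)) + 0.842·√(2·0.57·0.43 + 0.77·0.23)]² / (2 × 0.20²), with p̄ = (0.57 + 2 × 0.77)/3 = 0.703. This gives 83.3, so about 250 in total, and 250 × 1.1 = 275, as stated.
- Stability, same formula with 69% and 89%: 60.0, so about 180 in total, and 180 × 1.1 = 198, as stated.

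**What the threshold alone does to union.** If power is exactly 80% at 0.0167, the expected z is 2.394 + 0.842 = 3.236.

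- At 0.025: Φ(3.236 − 2.241) = 84.0%.
- At 0.05: Φ(3.236 − 1.960) = 89.9%.

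So 89.9% is the ceiling for Holm, and 84.0% is roughly what it reaches when only one other outcome is rejected.

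**How often the other two are rejected.** For NDI the expected z is 7.5 / (10 × √(1/82.5 + 1/165)) = 5.56, and Φ(5.56 − 2.394) = 99.9%. Stability has about 92% power at 0.0167.

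**Simulation** (165 v 83, independent outcomes, rates as above):

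| True effects | Union power, Bonferroni | Union power, Holm |
|---|---|---|
| All three at design size | 80% | 89% |
| Stability null | 80% | 84% |
| NDI null | 80% | 84% |
| Both null | 80% | 80% (gain about 0.1 point) |
| Union differs by 41 points | about 100% | about 100% |

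With all three effects at design size, stability rises from 92% to 96%, and the chance that all three are significant from 74% to 87%. Under the full null the family-wise error is about 4.9% with either method.

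**Sensitivity.**

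- Correlation: with union at 78% v 58% (80.4% power under Bonferroni), Holm gives 89.8%, 89.6% and 89.3% at correlations 0, 0.3 and 0.6.
- NDI effect: with stability at design size, an NDI difference of 5 points leaves a union gain of 8 to 9 points, and 3.5 points leaves 5 to 7.
- Union rates: if the conservative rate lies in the 28–44% range quoted in the Background, a 20-point difference has 72–74% power at 0.0167 and 85–87% at 0.05, so the largest possible gain there is 12 to 13 points.

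**False positives for one null outcome.** With the other two effects real, a null stability comparison is declared significant about 1.7% of the time under Bonferroni and about 4.5% under Holm. A null union comparison goes from about 1.7% to about 4.8%.

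**The case against.** The strongest reply is that nothing here is wrong. The sizing and the analysis use the same level, Bonferroni controls the family-wise error, and the trial keeps the 80% power for union that it planned. That stands. A reader might infer that the plan is underpowered or mishandles multiplicity, and the article supports neither reading.

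A reader might also take 9 points as what is always lost. That needs design-size effects on both other outcomes. The 7.5 NDI points are a minimal important difference, not a forecast, and the Background says the data are too few to establish a difference in clinical outcome. Union is also the tightest outcome only at 20 points: at the quoted 41 points its power is near 100% under either rule.

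Nor is it right that the fixed level buys nothing. It keeps a single null outcome at 1.7%, where Holm lets it rise to just under 5%. It also gives intervals that match the tests, whereas a 98.3% interval can include no difference for an outcome that Holm declares significant.

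Finally, treatment is chosen by surgeon and patient and the primary tests are unadjusted, so a threshold rule has limited weight beside confounding. This lowers the priority of the change. It does not remove the advantage, since Holm never rejects less than Bonferroni at the same family-wise error.

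**Conclusion.** The point holds as an inexpensive gain in efficiency, not as an error. For union the gain runs from about 0 to about 9 points: about 9 if stability and NDI both differ by their design amounts, about 4 if one of them does not differ, about 0 if neither does, and nil at a 41-point union difference. In the all-effects case the chance of significance on all three rises by 13 points (74% to 87%), which bears on the Sample size section's aim of a reliable conclusion on each comparison.

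The figures rest on 10% drop-out, the 2:1 split and back-solved rates. The union gain depends little on those rates, because it follows mainly from having 80% power at 0.0167.

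**What to change.** In the Univariate analysis section, replace the fixed 0.0167 on the primary tests with a sentence such as: the three primary hypotheses (union, stability, NDI improvement) will be tested with Holm's step-down procedure at an overall two-sided level of 0.05, the ordered p-values being compared with 0.0167, 0.025 and 0.05 and testing stopping at the first that fails. Make the change before outcome data are seen. Leave the target at 275 and describe its Bonferroni basis as conservative.

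The cost is one sentence and no patients. Two consequences should be accepted openly. The false-positive rate for a single null outcome can approach 5%, with the family-wise error still held at 5%. If 98.3% intervals are reported, some may include no difference for an outcome declared significant, so the report should say that the decisions rest on the Holm-adjusted p-values.

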Furthermore, the goal of treatment is still debatable. It is unknown whether or not non-union always leads to complaints in the patient. Consequently, debate remains as to whether the goal of treatment should be osseous union, fracture stability or a favourable clinical outcome. The measurement of these parameters is likewise not uniformly described. The available literature shows higher osseous union rates in surgically compared to conservatively treated patients (66–85% and 28–44%, respectively), but patient selection mechanisms may have profoundly interfered with these outcome percentages. The majority of patients achieved fracture stability regardless of the applied treatment (82-97% in surgically treated patients and 53-79% in conservatively treated patients). There are insufficient data available, especially from direct comparisons, to determine the difference in clinical outcome between surgical and conservative treatment strategies. There is no evidence that clinical outcome correlates better to fracture union than to fracture stability, or that the quality of union, whether it be osseous of fibrous, influences clinical outcome [12].

The goal of this study is to prospectively compare fracture union, fracture stability and NDI improvement at 52 weeks between surgical and conservative treatments in patients over 55 years of age with acute type II and III odontoid fractures. Predefined subgroup analysis may offer prognostic factors that can predict the success of either a surgical or conservative treatment. The influence of age (≥55-80 and ≥80 years) on treatment outcome will particularly be studied. The outcome of this study will yield valuable information enabling more rational decision making in treating the elderly patient population.

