### Withdrawal of individual subjects

Subjects can leave the study at any time for any reason if they wish to do so without consequences. As this is an observational study, this will only have influence on the study related assessments. Individual subjects withdrawn from the study will not be replaced. In the sample size a dropout rate of 10% was calculated for.

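### The 80% power claimed for a 20-point difference in union at 275 recruits does not hold at the article's own conservative union rates (28–44%), where it is 72–74%

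*Protocol article*

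**What the plan says.** The Sample size section sets aside the literature difference in union of 41 percentage points and says that "a smaller difference of 20% would be clinically relevant and the study is powered to assess this difference". It lists two-sided alpha 0.05/3 = 0.0167, 80% power, a 10% drop-out allowance and an expected 2:1 split of surgical to conservative patients. The resulting size "is 275 for union, 198 for stability and 93 for the NDI", and the largest figure, for union, becomes the recruitment target.

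That section gives no union rate for either group. The only rates are in the Background, which reports "higher osseous union rates in surgically compared to conservatively treated patients (66–85% and 28–44%, respectively"), and warns that patient selection may have affected them. On losses, the section on withdrawal says only "In the sample size a dropout rate of 10% was calculated for", without the method.

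**The concern.** A 20-point difference between two proportions does not fix a sample size until one of the two rates is fixed, because the variance depends on where the pair lies. The closer the rates are to 50%, the more patients are needed. If the 275 rests on a pair away from the middle, and the conservative rates in the Background imply a pair near the middle, the stated 80% is too favourable.

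Union drives the size of the study. If union came out null, readers would judge that result against a type II error of 20% for the difference called clinically relevant. At the article's own conservative rates the type II error is 26–28%.

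**Working it through.** **Inputs.** From Sample size: alpha 0.0167 two-sided (z = 2.394), power 80% (z = 0.842), d = 0.20, k = 2 surgical patients per conservative patient, drop-out 10%. From Statistical analysis: a chi-square test at alpha 0.0167. From Background: union 28–44% conservative, 66–85% surgical.

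**Formula** (pooled-variance two-proportion test; c = conservative, s = surgical):

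n_c = [2.394·√(p̄(1−p̄)(1+1/k)) + 0.842·√(p_c(1−p_c) + p_s(1−p_s)/k)]² / d², with p̄ = (p_c + 2p_s)/3 and total N = 3n_c.

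**Step 1: reproduce 275.** Try 57% v 77%. Then p̄ = 0.7033, the two terms are 1.3393 and 0.4861, n_c = 1.8254²/0.04 = 83.3, and N = 249.9. With drop-out as ×1.1 this is 274.9; as /0.9 it is 277.7. At 57.5% v 77.5%, N = 247.7 and 247.7/0.9 = 275.2. So 275 is reached at a conservative rate of about 57–58%, whichever drop-out method is used. The other solution is about 19–20% conservative (19.3% with /0.9, 19.9% with ×1.1). A continuity correction moves the upper solution to about 62% and the lower to about 15%. All of these lie outside 28–44%; 57% is 13 points above the top of that range.

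**Step 2: the article's conservative rates, surgery 20 points higher.** With 275 recruits and 10% loss, 275 × 0.9 = 247.5 are evaluable, so n_c = 82.5. Power is Φ(z), where z = [d√n_c − 2.394·√(p̄(1−p̄)·1.5)] / √(p_c(1−p_c) + p_s(1−p_s)/2). Example at 36% v 56%: (1.8166 − 1.4659)/0.5946 = 0.590, so power is 72.2%.

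| Conservative v surgical | Evaluable for 80% | Recruits (/0.9, rounded up) | Power with 275 recruits |
|---|---|---|---|
| 28% v 48% | 277.8 | 309 | 74.3% |
| 36% v 56% | 290.0 | 323 | 72.2% |
| 38% v 58% (minimum power) | 290.7 | 323 | 72.1% |
| 44% v 64% | 287.0 | 319 | 72.9% |
| 57% v 77% | 249.9 | 278 | 79.6% |

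No rate in 28–44% gives 275 with the printed inputs. Over that range, with drop-out as /0.9, unpooled variance needs 287–317 recruits and a continuity correction 334–350.

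**Step 3: start from the surgical rates instead.** With surgical union at 66–85% and conservative 20 points lower, power is 73.5% (66% v 46%), 79.6% (77% v 57%) and 87.0% (85% v 65%).

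**Step 4: both rates inside their quoted ranges.** The smallest gap is 66 − 44 = 22 points, so no 20-point pair fits both ranges. Power is 82.3% at 44% v 66%, 98.5% at 36% v 66%, and close to 100% at 36% v 77% (41 points).

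**Step 5: detectable difference.** Solving the Step 2 expression for d at 80% power gives 21.2 points at conservative 28%, 21.6 at 36% and 21.5 at 44%.

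**Step 6: the other two figures.** Stability at 69% v 89% gives 180.1 evaluable and 198.1 with ×1.1; about 69.3% v 89.3% gives 198 with /0.9. Both pairs lie inside the stability ranges in the Background (53–79% and 82–97%). For the NDI (7.5 points, SD 10), N = 3 × 1.5 × (2.394 + 0.842)² × 100/56.25 = 83.75, and 83.75/0.9 = 93.06. Rounding to 84 first, 84 × 1.1 = 92.4, also 93 when rounded up.

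**The case against.** Four points can be made on the other side.

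- **The ranges cannot both be met at 20 points.** One end had to give, and 77% surgical lies inside 66–85%. The Background also warns that selection may have distorted these percentages. This stands, and it means that 57% is not an error in itself. It does not rescue a flat 80%: the article gives no reason to expect 57% union under conservative treatment, and its own figures say otherwise.
- **If the literature is right, the study has ample power.** This is true for 22 points or more between rates inside both ranges. But the article claims power for the smaller, 20-point difference.
- **The practical effect is small.** This also stands. The difference detectable with 80% power moves from 20 to about 21–22 points.
- **An article condenses the protocol, and the base rate may be in the full version.** Possibly. The point is not that a detail is absent, but that the printed power fails at the only conservative rates printed.

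A reader might also infer that the 10% drop-out was wrongly applied as ×1.1, because the whole-percent pairs 77/57 and 89/69 return 274.9 and 198.1. The article does not support that. Division by 0.9 also gives 275 (at 57.5%), 198 (at 69.3%) and 93. At 57% the choice of method is worth about 3 recruits or 0.4 points of power, and the fall to 72–74% comes from the base rate. Nor may 77% v 57% be taken as the rates that the authors used; that is a back-calculation.

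**Conclusion.** The point holds for union. With the stated alpha, allocation and drop-out, 275 recruits give 72–74% power for a 20-point difference when conservative union is 28–44%. They give about 80% only near 57–58%, or near an implausible 19–20%. Measured from the surgical range the figure is about 73–87%, so the power depends on a rate that the article does not name.

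This rests on the pooled chi-square calculation, exactly 10% loss and a realised 2:1 split. It does not show that the study is too small for differences as large as those in the literature, or that recruitment must rise. An error in the drop-out allowance is not shown.

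**What to change.** 1. State the union and stability rates actually assumed in the sample size calculation, and reconcile the union rates with the Background.
2. Replace the flat 80% for union by power at named base rates (72–74% at conservative 28–44%, about 80% at 57%). Alternatively, state the difference detectable with 80% power at 28–44%, about 21–22 points.
3. Say whether the 10% drop-out was applied as ×1.1 or /0.9.

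The cost is wording and a slightly less favourable power statement, with no change in enrolment.

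Optionally, test the three primary outcomes with the Holm procedure at family-wise 0.05 instead of a fixed 0.05/3. It is never less powerful. In simulation at about 247 evaluable patients with union at 56% v 36%, union power rises from about 72% to 76–84%. That gain appears only if stability (simulated at 89% v 69%) and/or the NDI (7.5 points) also differ; if neither does, there is none. The price is less simple simultaneous confidence intervals. The fixed split is valid as it stands, so this is a choice and not a correction.
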